#### Randomization and blinding

2.3.2

Randomization is standardized in this study in combination with the design characteristics of the three parts of the experiment: The first part is a case–control observational study. After screening through strict inclusion and exclusion criteria, the case group (patients with lumbar muscle strain) and the control group (healthy people without lumbocrural pain) are selected from the eligible population by simple random sampling (15 cases in each group) to ensure sample representativeness, with no inter-group random allocation involved. The second part is a cross-over design study, in which 24 patients with lumbar muscle strain are divided into 3 groups (8 cases in each group) by complete randomization, receiving three sequences of rolling manipulation intervention with low-medium-high, medium-high-low and high-low-medium pressure, respectively. The third part is an interventional trial involving 69 participants in total. 46 patients with lumbar muscle strain are stratified by age and disease duration and then divided into a case intervention group (rolling manipulation intervention, *n* = 23) and a case control group (health education intervention, *n* = 23) by the random number table method; additionally, 23 healthy controls are selected by simple random sampling.

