
**Figure 2 fig2:**
[figure not shown]
fNIRS probe placement and channel distribution map. Three-dimensional and two-dimensional representations of fNIRS channel distribution. **(A)** Three-dimensional model showing cortical regions and fNIRS channel distribution. **(B)** Two-dimensional channel distribution model. L, left; R, right; LPFC, left prefrontal cortex; RPFC, right prefrontal cortex; LSMA, Left supplementary motor area; RSMA, right supplementary motor area; LSM1, left primary motor cortex; RSM1, right primary motor cortex; LSAC, left somatosensory association cortex; RSAC, right somatosensory association cortex.

Surface electromyographic signal detection (Part 2): The primary outcomes are the changes in sEMG RMS and MF from before to immediately after each rolling manipulation session. The primary comparison is the difference in these changes among the low-pressure, medium-pressure, and high-pressure conditions within the same participants. We hypothesize that the three pressure levels produce different immediate sEMG responses. The Noraxon Ultium surface electromyography system was used. The subjects took a prone position, and the electrode patches were attached to the marked points of the bilateral lumbar erector spinae and quadratus lumborum. The sEMG signals were recorded before and immediately after each rolling manipulation session with different pressure levels. The time-domain indicator (RMS) and the frequency-domain indicator (MF) were selected as the primary electromyographic outcomes for identifying the optimal pressure level. The RMS reflects the intensity of muscle activation, and the MF reflects muscle fatigue status.

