### Sample size calculation

2.8

Based on the core research objectives and design types of the three parts, this study is overall planned as follows:

The first part is an observational study, with the fNIRS-derived cortical hemodynamic response (HbO/HbR changes) as the primary outcome. Based on repeated measures analysis of variance (effect size *f* = 0.286, α = 0.05, 1−β = 0.8) (30), G*Power 3.1.9.7 calculation showed that 12 cases are needed in each group. Considering a 20% attrition rate, 15 cases are included in both the healthy control group without lumbocrural pain and the lumbar muscle strain case group, with a total of 30 cases.

The second part is a cross-over design. The sample size was estimated based on the median frequency (MF) of the surface electromyographic (sEMG) signals, one of the primary electromyographic outcomes for screening the optimal pressure. Referring to our previous study on rolling manipulation in patients with lumbar muscle strain (13), the within-individual standard deviation of sEMG frequency was 17.09 Hz and the intraclass correlation coefficient was 0.5. Repeated Measures ANOVA combined with Greenhouse–Geisser corrected F test (α = 0.05, 1-β = 0.8) was adopted. PASS 2021 software calculation showed that 17 cases are needed. Considering a 20% attrition rate, 24 patients with lumbar muscle strain are included and randomly divided into 3 group sequences.

The third part took the change in the Oswestry Disability Index (ODI) from baseline to immediately after the 6th intervention as the primary clinical endpoint for the comparison between the case intervention group and the case control group. Based on a two-independent-sample design, in which the expected between-group difference (μ2 − μ1 = 10) and the standard deviation (σ = 9) were derived from a previous study on massage combined with functional exercise for chronic lumbar muscle strain (31), With α = 0.05 and 1 − β = 0.80, the calculation showed that 18 patients were required in each group. Considering a 20% attrition rate, 23 patients with LMS will be enrolled in the case intervention group and 23 in the case control group, resulting in a total of 46 patients with LMS. In addition, 23 healthy controls will be enrolled as a reference group for the fNIRS and biomechanical comparisons. Therefore, Part 3 will include 69 participants in total, comprising 46 patients with LMS and 23 healthy controls.

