### Statistical analysis

2.10

Statistical analyses will be performed using MATLAB R2024b. fNIRS preprocessing and calculation of HbO/HbR concentrations, functional connectivity (FC), wavelet amplitude (WA), and graph-theoretical measures will be performed using NirSpark V1.8.9. Normally distributed continuous variables will be expressed as mean ± standard deviation, non-normally distributed variables as median and interquartile range, and categorical variables as frequencies and percentages. Normality will be assessed using the Shapiro–Wilk test. *p* < 0.05 will be considered statistically significant.

Baseline data: Baseline variables will be analyzed according to variable type, data distribution, and the number of groups using the t test, analysis of variance (ANOVA), Mann–Whitney U test, Kruskal-Wallis test, or chi-square test, as appropriate.

fNIRS data: Task-related fNIRS data will be analyzed using the general linear model (GLM) implemented in NirSpark to obtain channel-wise HbO and HbR β coefficients for subsequent group comparisons. To reduce the risk of false-positive findings arising from multiple comparisons, statistical tests of channel-wise activation will be corrected using the false discovery rate (FDR). Functional connectivity (FC), wavelet amplitude (WA), and graph-theoretical measures calculated in NirSpark will be exported for subsequent statistical analysis using linear mixed-effects models (LMM), with Bonferroni correction applied to multiple comparisons.

Biomechanical and clinical data: Repeatedly measured sEMG, muscle tension, pressure pain threshold (PPT), VAS, and ODI outcomes will be analyzed using repeated-measures ANOVA when the data are normally distributed. For non-normally distributed repeated measurements, generalized estimating equations (GEE) will be used in Parts 1 and 3, whereas the Friedman test will be used for the low-pressure, medium-pressure, and high-pressure conditions in Part 2. Bonferroni correction will be applied where multiple comparisons are required.

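### The Part 2 crossover analysis names no period term, and its Friedman fallback cannot hold one, so a period effect on the sEMG change would inflate the error and, with unequal sequences, shift the pressure contrasts

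*Protocol article*

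**What the plan says.** Section 2.3.2 describes the allocation: "24 patients with lumbar muscle strain are divided into 3 groups (8 cases in each group) by complete randomization". The section then names the three orders in which the pressures are given, with patients "receiving three sequences of rolling manipulation intervention with low-medium-high, medium-high-low and high-low-medium pressure, respectively". Each pressure therefore appears once in each of the three sessions, which is a cyclic Latin square.

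Section 2.5.2 takes the pre-to-post change in sEMG RMS and MF at each session as primary: "The primary comparison is the difference in these changes among the low-pressure, medium-pressure, and high-pressure conditions within the same participants".

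For the analysis, section 2.10 groups the sEMG measures with muscle tension, PPT, VAS and ODI in one rule, which ends: "ODI outcomes will be analyzed using repeated-measures ANOVA when the data are normally distributed". If they are not, "whereas the Friedman test will be used for the low-pressure, medium-pressure, and high-pressure conditions in Part 2". The factors of the ANOVA are not listed. Mixed models are planned only for the fNIRS connectivity, wavelet and graph measures, and GEE only for Parts 1 and 3.

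Section 2.8 sizes Part 2 on the same family of test: "Repeated Measures ANOVA combined with Greenhouse–Geisser corrected F test (α = 0.05, 1-β = 0.8) was adopted". The resulting number is given in the next sentence: "PASS 2021 software calculation showed that 17 cases are needed". Neither period nor sequence is mentioned as a model term anywhere. The one crossover safeguard is the 7-day washout, which sections 2.4.2 and 2.7 justify against carryover.

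**The concern.** A washout deals with carryover. It does not deal with a period effect, meaning a response that differs between the first, second and third session whatever the pressure. The Latin square makes period separable from pressure, but only if the analysis uses it.

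A test that compares pressures within participants and ignores period treats the three values of a person as exchangeable when pressure has no effect. A period effect breaks that. With equal sequences it averages out of the contrasts and lands in the residual, so the test becomes conservative. With unequal sequences some of it also stays in the contrasts.

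At stake is the choice of the Part 3 pressure. Section 2.4.2 sends only outcomes with significant differences across pressures on to the regression step, so a conservative test can keep a useful outcome out of that step.

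**Working it through.** **Inputs.** Three sequences of 8 (section 2.3.2); alpha 0.05, power 0.80, 17 completers, 20% attrition, 24 enrolled (section 2.8). Section 2.8 also states that "the within-individual standard deviation of sEMG frequency was 17.09 Hz and the intraclass correlation coefficient was 0.5". No detectable MF difference and no period effect are given, so both are assumptions here.

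**The plan's own figure.** The 17 cannot be reproduced without a difference, so I solved backwards. With F on 2 and 2(N−1) df and noncentrality N·Στ²/σ², sphericity assumed, 80% power at N = 17 needs Στ²/σ² = 0.623. As a linear low-to-high difference, that is 2·√(0.623/2) = 1.116 within-person SD. This equals 19.1 Hz if 17.09 Hz is the within-person error SD, or 13.5 Hz if it is the SD per measurement with correlation 0.5. Enrolment is consistent: 17/0.8 = 21.25, so 22, and the next multiple of 3 is 24. At N = 24 the same effect gives 92.8% power.

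**Error inflation, equal sequences.** Take a linear trend of t within-person SD per session, so period effects are −t, 0, +t. Without a period term:

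MSE/σ² = 1 + N·Σπ²/(2(N−1)) = 1 + N·t²/(N−1).

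At N = 24 and t = 0.5 this is 1 + 24 × 0.25/23 = 1.26.

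**Power at 8/8/8** (simulation with normal errors and the effect above):

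| t (SD per session) | MSE/σ² | ANOVA, no period | With period | Friedman |
|---|---|---|---|---|
| 0 | 1.00 | 0.93 | 0.93 | 0.83 |
| 0.25 | 1.07 | 0.92 | 0.93 | 0.80 |
| 0.5 | 1.26 | 0.87 | 0.93 | 0.73 |
| 0.75 | 1.59 | 0.79 | 0.93 | 0.60 |
| 1.0 | 2.04 | 0.63 to 0.65 | 0.93 | 0.42 |

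Entries are good to about one point. The ANOVA type I error without period falls from 5% to about 4%, 2.5% and 1% at t = 0.25, 0.5 and 0.75. With period in the model it stays near 5%.

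**Power at 17 completers, 6/6/5, t = 0.5.** ANOVA without period about 0.73, with period about 0.80.

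**Bias with unequal sequences.** Let n1, n2, n3 complete low-medium-high, medium-high-low and high-low-medium. High falls in sessions 3, 2, 1 and medium in sessions 2, 1, 3. The unadjusted high-minus-medium contrast is therefore shifted by

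t·(n1 + n2 − 2·n3)/N.

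- 8/8/8: 0.
- 6/6/5: (12 − 10)/17 = 0.12·t, or 0.06 SD at t = 0.5.
- 8/7/4 (illustrative): (15 − 8)/19 = 0.37·t, or 0.18 SD at t = 0.5.

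With period in the model the bias is zero at any split. Because 17 is not divisible by 3, the sequences cannot be equal at that number.

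**Cost of the period term.** It takes 2 error df. With no period effect and balanced sequences, power moves from 80.0% to 79.7% at N = 17 and from 92.8% to 92.7% at N = 24.

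**The case against.** The best defence has four parts.

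- **The ANOVA terms are not listed.** A condensed article may leave them to a fuller document, which could include period. This stands. A reader might infer that the main test is fixed as one-way by pressure, but the only one-way ANOVA named is in section 2.4.2, for the calibration force values. What is fixed without period is the Friedman fallback, which no fuller document can amend by adding a term.
- **The outcome is a change within each session.** A week-to-week drift in level, from practice or natural recovery, cancels. This stands too: only a drift in the acute response matters, and nothing in the documents shows that one exists. It relies on a fresh pre-measurement at every session, as sections 2.5.2 and 2.5.3 describe.
- **The square is balanced.** With equal sequences the contrasts are unbiased and the test errs on the safe side. That is correct. A reader might infer confounded contrasts or inflated false positives from the design itself; equal sequences give neither. With unequal sequences, power without period can move either way: at 8/6/3 and t = 0.5 it is about 0.87 against 0.76 with period, and the excess comes from bias.
- **Significance does not decide the choice alone.** Section 2.4.2 uses it to admit outcomes to the regression, and the pressure is then chosen on the overall pattern. A reader might infer that non-significant outcomes leave the selection altogether, but the text does not say so.

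The Friedman column also needs care. Its deficit at t = 0 (0.83 against 0.93) has nothing to do with period, and the errors simulated are normal, whereas the plan uses Friedman only for non-normal data.

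**Conclusion.** The point holds as an inexpensive improvement whose benefit is conditional. The crossover is randomised by sequence, but its stated analysis names no period term and its fallback cannot take one.

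The size depends wholly on a period effect in the acute response that the documents do not give. With 24 completers and the planning effect, the ANOVA loss is about 1 to 2 points at a trend of 0.25 SD per session, 5 at 0.5, 13 to 14 at 0.75 and about 30 at 1.0. The upper values are large: 0.5 per session already means a shift of 1 SD from the first to the third session. A loss of 20 points or more should not be read as the expected case, since at 8/8/8 it needs a trend above 0.75. The bias at 6/6/5 is small; 8/7/4 is an unfavourable example, not a forecast.

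The results assume a linear trend, normal errors, sphericity and an effect back-solved from the 17 completers.

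**What to change.** In section 2.10, for RMS and MF change and the other Part 2 outcomes, specify a linear mixed model with pressure and period as fixed effects and participant as a random effect. A sequence term is optional. Replace Friedman with a fallback that respects period: the same model on transformed or ranked values, or a permutation test that re-randomises participants over the three sequences.

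This is a change of wording, with no extra patients or measurements, and mixed models are already in the plan for fNIRS. It spends two degrees of freedom. With no period effect the power loss is about 0.3 points or less when sequences are equal or nearly so. It grows with imbalance, to about 3 points at 8/6/3 (0.79 to 0.76).

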## Discussion

3

This study establishes a three-part research framework integrating pain stimulation, cortical hemodynamic responses, manipulation parameter optimization, and clinical efficacy evaluation. By combining functional near-infrared spectroscopy and biomechanical assessments, this study aims to investigate cortical hemodynamic responses associated with lumbar muscle strain pain, identify biomechanically favorable pressure parameters for rolling manipulation, and explore the potential association between peripheral biomechanical responses and cortical hemodynamic changes during treatment. This study may provide preliminary evidence for the standardization and further development of Tuina manipulation.

This study adopted a controlled design to investigate differences in cortical hemodynamic responses between patients with lumbar muscle strain and healthy individuals under different intensities of painful stimulation. The research approach of this experiment is somewhat consistent with current research directions on the central regulation of chronic musculoskeletal pain, and has a certain theoretical and research foundation. Previous studies have confirmed that chronic musculoskeletal pain could induce significant changes in brain structure and function, typically manifested as decreased functional connectivity in the prefrontal cortex and abnormal spontaneous brain activity (32), as well as hemodynamic abnormalities in pain-related brain regions such as the primary motor cortex and somatosensory cortex (33). These changes are consistent with the theory of central sensitization, where persistent nociceptive input leads to hyperexcitability and functional reorganization of central pain-processing pathways (34). The prefrontal cortex and its subregions exerted multiple functions in pain processing, including nociceptive localization, attention allocation, and emotional modulation, and mostly showed significant activation under painful stimulation (35–37). By using graded pain stimulation and fNIRS, this study will systematically analyze the correlation between lumbar muscle strain pain and brain activation, examining cortical response characteristics associated with lumbar muscle strain pain and identifying cortical regions associated with pain processing in lumbar muscle strain.

This study graded and screened the pressure parameters of the rolling manipulation from a biomechanical perspective, aiming to overcome the subjective limitations of traditional tuina that relies on empirical operation. Existing studies have shown that the core mechanism of massage-like manipulations is closely related to mechanotransduction: mechanical pressure act on the skin, fascia and muscle tissues, and regulate inflammatory responses and pain regulatory pathways through cellular signal transduction (38). The therapeutic effect of manipulations does not simply depend on the magnitude of force, but on the standardized combination of pressure, frequency and duration, and a stronger pressure does not necessarily lead to a better effect (38–40). Studies on tuina for peripheral induced neuropathic pain have also confirmed that appropriate manual stimulation can exert analgesic effects through peripheral anti-inflammation, regulating ion channels and altering central brain function (41). Accordingly, this study defined low, medium and high levels based on individualized pressure calibration combining VAS perception and objective pressure measurements. Optimal parameters are selected using multi-dimensional biomechanical indicators including surface electromyography and isokinetic muscle strength, and standardized monitoring of manipulation parameters is realized via a dynamic pressure distribution measurement system. It is intended to establish a quantitative correlation system of “individual pain threshold-manipulation mechanical parameters-biological effect”, so as to formulate an objective and repeatable pressure standard for the rolling manipulation and solve the key problem of the lack of quantitative specifications for clinical tuina parameters.

The application of fNIRS technology in monitoring cortical hemodynamic responses during Tuina intervention takes advantage of the unique features of this technology and provides a new methodological approach for investigating cortical responses associated with Tuina manipulation. At present, a variety of functional neuroimaging technologies have been proven to be applicable to the research of brain pain perception (42). With the advantages of portability, low cost and robustness against motion artifacts, fNIRS is more suitable for real-time and dynamic monitoring in clinical scenarios (43) and has successfully realized the quantitative detection of pain-related brain region activation in studies such as myofascial pain syndrome (44). Existing fNIRS studies related to tuina have confirmed that tuina could regulate the blood oxygen levels of brain regions such as the prefrontal cortex and sensorimotor cortex to achieve central regulation of motor nerves and pain perception (45, 46). However, fNIRS-based investigations of cortical hemodynamic responses during Tuina treatment for musculoskeletal disorders such as lumbar muscle strain remain limited. Dynamic monitoring of changes in cerebral blood oxygen before, during and after pain stimulation and rolling manipulation intervention by fNIRS could capture the real-time cortical hemodynamic response, and preliminarily characterize the cortical hemodynamic responses of rolling manipulation in the treatment of lumbar muscle strain, and evaluate the potential utility of fNIRS as an objective monitoring tool for tuina-related cortical hemodynamic responses. Continuous physiological signals such as heart rate, blood pressure, and respiration are not recorded synchronously during fNIRS acquisition; therefore, systemic and extracerebral hemodynamic contributions cannot be fully excluded. Accordingly, HbO/HbR changes in this study will be interpreted as cortical hemodynamic responses associated with the experimental conditions rather than as direct measures of neuronal activation.

The multidimensional evaluation framework, integrating biomechanical assessments, fNIRS-derived cortical hemodynamic responses, and clinical efficacy indicators, provides a comprehensive approach to explore the relationship between peripheral biomechanical responses and cortical changes associated with rolling manipulation. This framework may contribute to further understanding of the potential mechanisms underlying Tuina effects. Existing studies have confirmed that tuina manipulations could activate peripheral mechanoreceptors and transmit signals to the central nervous system through repeated therapeutic touch, which could not only induce immediate acute changes in brain function to achieve short-term analgesia and relaxation, but also drive the brain to undergo neural plastic adaptation, reshape the pain regulation circuit, and realize the lasting recalibration of central function (40, 47). Simultaneous assessment of peripheral biomechanical indicators, fNIRS-derived cortical hemodynamic responses, and clinical efficacy indicators enables exploratory analysis of the relationships among peripheral responses, cortical changes, and clinical outcomes. This approach may provide preliminary evidence for understanding the biological responses associated with rolling manipulation and contribute to the scientific interpretation of TCM Tuina.

Although this study has significant advantages in research design and technology integration, there are still potential limitations based on the current technological development and research conditions: Restricted by the inherent characteristics of fNIRS technology, it could only detect changes in cerebral cortical blood oxygen concentration and could not explore the functional changes of subcortical pain-related nuclei such as the thalamus and amygdala, which might lead to an incomplete characterization of subcortical pain-related processes (48). The study intended to screen the optimal parameters using low, medium and high force levels, but has not yet conducted an in-depth exploration of the precise force values and pressure distribution within the optimal level, and it is necessary to improve the individualized adjustment scheme of manipulation parameters in the future. The single-center study design results in a relatively high homogeneity of the enrolled population, and even if the sample size is scientifically estimated and the attrition rate is reserved, the extrapolability of the research results may still be affected to a certain extent. The case control group in this study receives health education, with the aim of evaluating the clinical effect of optimal-pressure rolling manipulation relative to health education. The present study does not separately address the effects of treatment time, physical contact, placebo effects, or other nonspecific factors. In addition, the treating practitioner cannot be blinded to the intervention being delivered, which is an inherent limitation of manual therapy trials. This potential performance bias will be mitigated by blinding the outcome assessors and data analysts.

Based on the design idea and potential limitations of this study, combined with the current research progress, follow-up extended research could be carried out in various aspects. Ultrasound elastography could be used to assess changes in lumbar soft tissue stiffness before and after rolling manipulation, providing direct biomechanical evidence for the therapeutic effects of the intervention. In addition, if it is confirmed that fNIRS could effectively detect brain function changes under rolling manipulation intervention, multi-modal neuroimaging research could be further carried out in combination with fMRI and EEG to make up for the deficiency of insufficient detection depth of fNIRS and comprehensively investigate the cortical–subcortical pain network involved in rolling manipulation responses. Machine learning technology is introduced to construct a prediction model for the curative effect of tuina in the treatment of lumbar muscle strain based on fNIRS brain function characteristics, realizing the precise evaluation of tuina treatment (32, 43). After screening out the optimal pressure parameters of rolling manipulation, multi-center, large-sample long-term follow-up clinical trials are carried out to verify the universality and long-term curative effect of the parameters, providing further evidence for evaluating the generalizability and clinical applicability of the parameters.

This hierarchical protocol integrates fNIRS and biomechanical assessments to investigate key scientific questions related to Tuina parameter optimization and cortical responses during intervention. If successful, this study will characterize cortical hemodynamic response patterns associated with LMS pain, identify biomechanically supported pressure parameters for rolling manipulation, explore the potential association between peripheral biomechanical responses and cortical hemodynamic changes during treatment, and evaluate the feasibility of applying fNIRS in Tuina research. The findings may provide preliminary evidence for the optimization of rolling manipulation parameters and a better understanding of biological responses associated with Tuina intervention.

